## Abstract

**Background:** Rising obesity rates among young adults increase long-term health risks, especially cardiometabolic conditions such as type 2 diabetes mellitus. Digital interventions can offer scalable solutions to promote and support healthy behaviors by integrating personalized diet, physical activity promotion, and behavioral support. **Objective:** To assess the feasibility, user friendliness, adherence, and satisfaction of the Healthy Lifestyle Recommender System (HLRS). Secondary outcomes will include measures of metabolic health and obesity. **Methods:** A 3-month, single-arm pilot study conducted across European countries, including Bulgaria, Germany, Italy, Netherlands, Portugal, and Spain, enrolling 351 young adults (18–25 years old, BMI 18.5–29.9 kg/m^2^). The intervention includes a mobile app for meal planning (Nutrida v.1), gamified physical activity encouragement (GameBus), and real-time monitoring via a wearable smartwatch device. Primary outcomes are adherence and engagement, measured through app usage and participant feedback; secondary outcomes include anthropometry, physical activity, dietary patterns, psychological well-being, and selected biomarkers of metabolic health. **Expected Outcomes:** Improved engagement is expected to enhance lifestyle behaviors, supporting weight management and overall well-being. Findings will guide future large-scale interventions. **Conclusions:** This study will contribute to minimizing the impact of obesity in Europe.

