### 2.2. Population: Inclusion and Exclusion Criteria

The pilot trial usually involves 30 young adults of both sexes per country; however, the final number of participants depends on each country, and there are a total of approximately 351 participants (Table 1). Inclusion criteria are age of 18–25 years, residence in the regions where the trials are conducted, BMI between 18.5 and 29.9 kg/m^2^ (normal weight to overweight), willingness to participate, ownership of a smartphone, and basic mobile application skills.

Exclusion criteria include individuals with obesity (BMI > 30.0 kg/m^2^), chronic conditions such as cancer, Parkinson’s disease, or other illnesses requiring specific treatments or significantly affecting normal physiology (e.g., metabolic disorders), cognitive impairments (e.g., Alzheimer’s disease), inability to live independently, adherence to specific diets, or inability to provide voluntary informed consent. However, individuals being treated for conditions such as type 2 diabetes, hypertension, or elevated blood lipids (e.g., triglycerides, cholesterol) will be included to ensure the recruitment reflects the typical demographic. If the drop-out or discontinuation rate exceeds 10%, additional participants will be recruited to maintain a minimum sample size of 20 participants per study site.

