## 3. Statistics

Sample Size Calculation: The study hypothesizes that the use of HLRS (≥45 min per week) will not decrease by more than 20% over the 3-month intervention period. Assuming a 30% standard deviation in usage, a 0.05 significance level, and 80% power, 20 participants would be required for a paired design. To compensate for an expected 33% attrition, 30 participants will be recruited, ensuring sufficient power. An equal distribution of males and females will be targeted to enhance the generalizability of the findings.

Handling of Missing Data and Dropout: No imputation will be performed for missing data. Participants who withdraw will be excluded from further analysis beyond their last available data. In order to maintain sample size and statistical power, replacements will be made as necessary, ensuring at least 20 participants complete the study. This method safeguards the integrity of the data and minimizes potential bias.

Data Analysis: Normality of the data will be assessed through Q-Q plots and Kolmogorov–Smirnov tests. Non-normally distributed data will be analyzed using non-parametric methods such as the Friedman test, followed by pairwise comparisons, and log transformations if appropriate. A significant level of *p* < 0.05 will be considered. Data will be analyzed using SPSS (version 25.0) and R (version 4.4.1). Since outcomes will be mainly descriptive, simple and descriptive statistics will summarize baseline participant characteristics, and changes over time will be assessed using paired t-tests, to evaluate the impact of the intervention on health outcomes.

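### The 20-completer, 30-recruit sample size is a per-site figure presented as the whole trial's, and Table 1 contradicts it at three of eight sites

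*Protocol article*

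**What the plan says.** Section 3 of the Protocol article (Sample Size Calculation) hypothesises that HLRS use "will not decrease by more than 20% over the 3-month intervention period". It continues: "Assuming a 30% standard deviation in usage, a 0.05 significance level, and 80% power", and concludes that "20 participants would be required for a paired design". Then: "To compensate for an expected 33% attrition", "30 participants will be recruited, ensuring sufficient power". The paragraph on missing data and dropout adds that replacements will be made, "ensuring at least 20 participants complete the study". None of these sentences says whether the number is for a site or for the trial.

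Other parts of the article give different sizes:

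- The Abstract describes the trial as "enrolling 351 young adults", and section 2.2 gives the same total.
- Section 2.2 also describes 30 per country as usual and sets a floor of 20 at each site, to be kept up by further recruitment.
- Table 1 lists, for eight sites, an enrolment target and a number of completers required.
- Table 3 gives an intervention length of 3 months at six sites, 1.5 months in Italy and 1 to 2 months in the Netherlands.

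**The concern.** The only power statement in the article belongs to a group of 20, while the trial described elsewhere is many times larger. A reader of section 3 alone cannot tell what the 80% refers to. If it is the trial, then 351 and 182 have no supporting calculation and the precision of the combined result is not given. If it is each site, Table 1 should require at least 20 everywhere, and it does not.

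The pilot is meant to lay the ground for a 12-month controlled study. Those who plan that study need to know how many participants the usage result rests on and how precise it will be.

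**Working it through.** **Inputs.** From section 3: margin 20 points, SD 30, alpha 0.05, power 80%, attrition 33%. From Table 1: the site numbers below. From Table 3: intervention lengths. Assumed, because the article does not say: 30 is the SD of the within-person change, the true change is zero, and the test is two-sided at 0.05 (for this purpose the same as one-sided at 0.025).

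**Step 1: reproduce the plan's figure.** For a paired t-test the noncentrality is (20/30) × √n. At n = 20 this is 2.98 and power is 80.7%, so 20 is the smallest n that reaches 80%. Attrition: 20 / (1 − 0.33) = 29.9, so 30. Both stated numbers are reproduced, for a single group.

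**Step 2: compare with Table 1.** Loss allowed = 1 − required/enrolled; power is at the required number.

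| Site | Enrolled | Required | Loss allowed | Power |
|---|---|---|---|---|
| Bulgaria | 30 | 20 | 33% | 81% |
| Germany | 30 | 15 | 50% | 67% |
| Italy | 101 | 52 | 49% | >99% |
| Netherlands | 40 | 20 | 50% | 81% |
| Portugal, UC | 30 | 15 | 50% | 67% |
| Portugal, UEV | 30 | 15 | 50% | 67% |
| Spain, CITA | 60 | 25 | 58% | 89% |
| Spain, IDISBA | 30 | 20 | 33% | 81% |
| Total | 351 | 182 | 48% | see step 4 |

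Only Bulgaria and IDISBA follow the 30-to-20 plan. At n = 15 the noncentrality is (20/30) × √15 = 2.58 and power is 67.1%.

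**Step 3: sensitivity to the assumptions.** With a one-sided test at 0.05, the required n is 16 and power at 15 is 79.1%. That reading does not give the plan's 20. If 30 is the SD at each time point, a correlation of 0.5 gives an SD of change of 30 and again n = 20. Lower correlations need more: 29 at 0.25 and 38 at zero.

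**Step 4: the combined sites.** The 95% half-width is t × 30/√n, before any allowance for site.

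- n = 20: 2.093 × 30/√20 = ±14.0 points.
- n = 182: 1.973 × 30/√182 = ±4.4 points.
- Required completers at sites that Table 3 lists with 3 months: 182 − 52 (Italy) − 20 (Netherlands) = 110. Half-width: 1.982 × 30/√110 = ±5.7 points.

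Power at 182 for the 20-point margin exceeds 99.9% if participants are independent. It stays at 99% or more with a site intraclass correlation of 0.01 to 0.10, a range assumed for illustration.

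**The case against.** The best defence is that section 2.2 supplies the missing unit. Its typical 30 per country and floor of 20 per site are the same numbers as in section 3, so the calculation is evidently a per-site one. That is right, and it rules out the literal reading that the completion rule is met once 20 of 351 participants finish. It does not settle the matter, because Table 1 requires fewer than 20 at three sites.

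The arithmetic of 20 and 30 is also sound, and combining sites only adds power. Both points stand: this is neither a calculation error nor an underpowered trial. Nor is the 67% a forecast. Thirty enrolled with 33% loss would leave 20; the 67% applies if a site concludes at its Table 1 minimum.

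A reader might go further and ask how often all eight sites would succeed (about 14% at the Table 1 minima, assuming independent sites). Or the question might be how often at least one site would pass if every site truly lost exactly 20% (18% at 0.025 each, 34% at 0.05 each). These figures are illustrative only. The article plans no such verdict and calls its outcomes mainly descriptive. The 14% also takes Table 1 over section 2.2: with 20 completers at the three small sites it becomes 0.807⁶ × 0.892 × 0.997, about 25%.

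Finally, the choice between combined and site-level analysis is often left to a SAP, which is not shown here. So the article gives no ground for saying that the level will be chosen after the data are seen. But no SAP can make the article's printed numbers agree with each other.

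**Conclusion.** The point holds as a mismatch between stated size, stated power and the trial described. Section 3 gives a per-site calculation without saying so. Table 1 breaks it at Germany and both Portuguese sites (15 required, about 67% power instead of 80%). It also allows 48% loss overall, 33% to 58% by site, against the planned 33%.

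The 67% rests on an SD of change of 30, no true change and a two-sided 0.05 test, which is the reading that returns the plan's 20. The Table 1 sums and the loss percentages need no assumption.

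A single combined precision figure cannot simply be inserted. The hypothesis covers three months, and 72 of the 182 required completers are at sites that Table 3 lists with shorter interventions. For a largely descriptive pilot this is a matter of correction and clarity. It does not threaten the trial's ability to answer its question.

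**What to change.** In section 3:

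1. State that 20 completers and 30 recruits are the calculation for one site, and give the trial totals: 351 enrolled and 182 required completers.
2. Reconcile the floor of 20 per site, the Table 1 entries of 15 and the 33% attrition. Either correct Table 1, or restate the power as about 67% at the three sites and give the loss that the table actually allows.
3. Replace the sentence on 20 participants completing with one that refers to the site numbers.
4. State that the usage hypothesis is judged on the combined sites, with site accounted for in the analysis and site results descriptive.
5. Give the expected precision at SD 30, before any allowance for site: about ±4.4 points for 182 completers, or ±5.7 for the 110 at sites listed with three months. Reconcile the three-month hypothesis with the intervention lengths in Table 3, so that it is clear which figure applies.

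The cost is a rewritten paragraph and, if that route is taken, corrected Table 1 entries. Enrolment targets do not change. Sites give up a separate confirmatory claim.

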### 2.7. Outcome Measures and Data Collection

Primary outcomes focus on adherence and user experience, measured by app usage frequency/duration and wearable device data. User experience is evaluated using validated tools such as the User Experience Questionnaire [20,21].

Secondary outcomes include anthropometric measures, biological markers, physical activity, and dietary patterns, assessed through wearables and validated questionnaires, as described below and summarized in Table 4.

Anthropometric measurements: Body weight, height, waist circumference, hip and thigh circumferences will be taken, and body composition will be conducted following standardized procedures, with specific equipment varying by country. Body weight will be recorded with participants wearing light clothing and no shoes. A predetermined weight will be subtracted to account for clothing. Height will be measured to the nearest millimeter with participants standing upright and maintaining the Frankfurt Horizontal Plane. Body mass index (BMI) will be calculated as weight (kg) divided by the square of height (m^2^). Waist circumference (WC) and hip circumference (HC) will be measured in duplicate using an anthropometric tape, ensuring proper positioning and participant posture. WC will be assessed at the midpoint between the lowest rib and the iliac crest, while HC will be measured at the widest part of the hips, with the tape placed horizontally around the body. Participants will stand upright with feet together, and the average of the two measurements will be recorded for analysis [22].

Biological samples: The participants may provide saliva, urine, and blood samples. Urine samples will be collected the day after completing a 24 h Recall (24hR) to accurately assess dietary biomarkers. Additional assessments, including markers of oxidative stress and inflammation (Table 4), will be performed using commercial ELISA kits according to the manufacturer’s instructions [23,24,25].

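### A start-to-end comparison of app use would rest on completers only, so it leans towards sustained use, and the plan wrongly says its dropout rule limits bias

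*Protocol article*

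**What the plan says.** Section 2.7 defines the primary outcomes: "Primary outcomes focus on adherence and user experience, measured by app usage frequency/duration and wearable device data". Section 3 gives the only quantified hypothesis, that "the use of HLRS (≥45 min per week) will not decrease by more than 20% over the 3-month intervention period". The inputs to the sizing are an SD of 30%, alpha of 0.05 and power of 80%, and the result given is that "20 participants would be required for a paired design". It expects 33% attrition and therefore recruits 30.

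The paragraph on missing data and dropout in Section 3 sets four things:
- Missing values are not imputed.
- On withdrawal: "Participants who withdraw will be excluded from further analysis beyond their last available data".
- On keeping up numbers: "replacements will be made as necessary, ensuring at least 20 participants complete the study".
- As its justification for these rules, the paragraph closes with: "This method safeguards the integrity of the data and minimizes potential bias".

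Section 2.2 adds a trigger: "If the drop-out or discontinuation rate exceeds 10%, additional participants will be recruited", with a floor of 20 per site. Nowhere does the article count withdrawal as non-use or say how it enters the adherence measure.

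**The concern.** For a blood marker, a value missing after withdrawal is unknown. For continued use of an app, leaving the study is often part of the answer. A paired change from start to end needs an end value. Withdrawers have none in the analysis, because nothing is imputed and they contribute nothing after they leave. The comparison is therefore made in people selected for staying, who are likely to be the more engaged.

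Replacement strengthens the selection. Recruitment goes on until enough people complete, so the number lost does not enter the usage result. Table 1 requires 20 completers from 30 enrolled in Bulgaria and 20 from 40 in the Netherlands. At those minimums each site supplies 20 pairs, although one would have lost a third of its participants and the other half.

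The pilot's objective is feasibility and adherence, and Section 2.1 says it lays the ground for a 12-month controlled study. An adherence figure conditional on retention would be too favourable a basis for planning that study.

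**Working it through.** **Inputs.** From Section 3: limit 20%, SD 30%, alpha 0.05, power 80%, 20 paired participants, attrition 33%, 30 recruited. From Table 1: enrolment targets and numbers required for completion. The 30% is read as the SD of the paired change, because that reading reproduces the plan's 20.

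**1. The plan's own figures.** For a two-sided paired test, the normal approximation gives n = ((1.960 + 0.842) × 30/20)² = 17.66, so 18. The exact noncentral t calculation gives 20, with power 80.7%. Attrition: 20/0.67 = 29.9, so 30. Both stated numbers reproduce, so the arithmetic is not at fault. It also confirms that the 20 are the people left after attrition, that is, completers.

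**2. Fall in use among all enrolled.** Let d be attrition, w the share of use that withdrawers lose, and y the completers' fall. If withdrawers and completers start from the same mean use,

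fall = d × w + (1 − d) × y.

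| d | w | y | fall among all enrolled |
|---|---|---|---|
| 33% | 100% | 0% | 33.0% |
| 33% | 100% | 10% | 33.0 + 6.7 = 39.7% |
| 33% | 100% | 20% | 33.0 + 13.4 = 46.4% |
| 33% | 50% | 0% | 16.5% |

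**3. Break-even.** With unchanged completers, the 20% limit is exceeded when w > 0.20/0.33 = 0.61. If withdrawers' use is zero, completers would have to raise theirs by 0.80/0.67 − 1 = 19% to hold the overall fall at 20%.

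**4. What the completers show.** Take 20 completers with mean change 0 and SD 30, and test against −20% at one-sided 0.025. The noncentrality is (20/30) × √20 = 2.98 and the probability of passing is 80.7%. A simulation of 50,000 runs gave 80.6%. This equals the power in step 1, because the two calculations are the same.

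**5. Worst case from Table 1.** Enrolment: 30 + 30 + 101 + 40 + 30 + 30 + 60 + 30 = 351. Required for completion: 20 + 15 + 52 + 20 + 15 + 15 + 25 + 20 = 182. If only those 182 completed, d = 169/351 = 48.1%. With unchanged completers the fall would be 48.1% at zero use after withdrawal and 24.1% at half loss, with break-even at 0.20/0.481 = 42%.

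**The case against.** Several stronger readings are tempting, and the documents do not support them.

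- **Withdrawers are discarded altogether.** They are not. Their data up to withdrawal are kept and can enter descriptive or interim summaries. Only the start-to-end comparison loses them.
- **The planned attrition already breaches the 20% limit.** This requires withdrawers to lose more than about 61% of their use, which the documents do not say. At half loss and 33% attrition the fall is about 17%, inside the limit.
- **The protocol has a pass rule that completers would meet.** It states none. Section 3 calls the outcomes mainly descriptive and ties the paired t-tests to health outcomes. The 81% comes from a test inferred from the sizing paragraph.
- **Table 1 forecasts 48% attrition.** The 182 are required minimums. The only attrition the article expects is 33%.
- **Replacement hides retention.** This is not shown. Section 2.2 monitors the drop-out rate, Table 1 separates enrolment from completion, and participant-flow reporting may sit in the full protocol.
- **Every withdrawal is non-adherence.** Section 4 provides for withdrawal over significant medical issues or distress, which is not rejection of the app. Leaving the study also differs from ceasing to use it.

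These objections limit the size of the problem but do not remove it. The usage hypothesis is itself sized as paired in 20 people, and the no-imputation, exclusion and replacement rules are stated in the text, not left open. The claim about bias is also stated, and it is mistaken for this outcome.

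**Conclusion.** The concern holds in a limited form. Under the stated rules, any start-to-end comparison of app use rests on completers and is biased towards sustained use. The sentence saying that the method limits bias should not stand. The direction of the bias rests on withdrawers using the app less than those who stay. Its size depends on how much less, which the documents do not give. At the expected 33% attrition with unchanged completers, the fall among all enrolled is about 17% if withdrawers lose half their use and 33% if they lose all of it, against 0% seen in completers. The 48% figure is a worst case at the Table 1 minimums.

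**What to change.** 1. Define the adherence analysis set as everyone given the HLRS at Day 0.
2. Count use after withdrawal as zero, or use logged use where consent permits. GameBus and Nutrida data sit on servers (Section 2.7), so no final visit is needed. Section 5 lets participants restrict processing or request deletion, so logs will not always be available.
3. Add a sensitivity analysis that treats medical withdrawals separately.
4. Add replacements to the denominator; do not substitute them for withdrawers.
5. Report retention out of all enrolled next to the usage result.
6. Keep the completers-only result as a sensitivity analysis.
7. Delete the sentence "This method safeguards the integrity of the data and minimizes potential bias".

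The cost is wording in Section 3 and an analysis of data already being collected, with no extra participants or visits. The reported adherence will look less favourable. Zero use after withdrawal is a conservative assumption that may understate use in people who leave the study but keep the app, so it should be labelled as such.

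### The normality check that chooses between paired t-test and rank method is not tied to the within-person changes, and a Kolmogorov–Smirnov p-value is a poor guide to that choice (minor)

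*Protocol article*

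**What the plan says.** The Data Analysis paragraph of Section 3 (Statistics) sets out a check, a consequence and a default test.

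- Check: "Normality of the data will be assessed through Q-Q plots and Kolmogorov–Smirnov tests".
- Consequence: "Non-normally distributed data will be analyzed using non-parametric methods such as the Friedman test, followed by pairwise comparisons, and log transformations if appropriate".
- Default: "changes over time will be assessed using paired t-tests, to evaluate the impact of the intervention on health outcomes".

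The paragraph begins its last sentence with "Since outcomes will be mainly descriptive, simple and descriptive statistics will summarize baseline participant characteristics". It does not say whether 'the data' are the measured values or the paired changes. It also leaves open what happens when plot and test disagree, which version of Kolmogorov–Smirnov (KS) is meant, and whether the check is made per site or pooled. Section 2.6 places data collection at the baseline and final visits.

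**The concern.** A paired t-test is a one-sample test on the within-person differences. Its validity depends on how those differences are distributed and, as n grows, only on their mean being close to normal. The spread of raw values between people does not enter. Cytokines, triglycerides or app minutes may well be skewed across people while their changes are symmetric, and the reverse can also occur. A check aimed at the wrong quantity can therefore discard a sound t-test or keep an unsound one.

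The named test adds a second difficulty. Standard KS critical values assume that the mean and SD are known in advance. When both are estimated from the sample, the uncorrected test hardly ever rejects at small n. Like any normality test, KS also gains power with n, just as the t-test's need for normality fades.

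At stake is the choice of method for each secondary outcome. Small n matters most for the cytokine and oxidative stress markers, which Table 4 assigns to one site (IDISBA), where Table 1 requires 20 completers.

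**Working it through.** **The plan's own figure.** Section 3 states "Assuming a 30% standard deviation in usage" and a margin under which usage "will not decrease by more than 20% over the 3-month intervention period", and concludes "a 0.05 significance level, and 80% power, 20 participants would be required for a paired design". Taking 30 as the SD of the paired change, the standardised effect is 20/30 = 0.667. Two-sided power from the non-central t distribution is 0.785 at n = 19 and 0.807 at n = 20, so 20 is reproduced. With attrition, 20/(1 − 0.33) = 29.9, or 30. Nothing below changes these numbers.

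**Sample sizes used.** n = 20 is the planning size. n = 52 is the largest site requirement (Italy, Table 1). n = 182 is the sum of required completers in Table 1: 20 + 15 + 52 + 20 + 15 + 15 + 25 + 20. It applies only if sites are pooled. The article gives no distribution shapes, so every shape below is an assumption. Results are simulated at the 5% level, mostly with 8,000 samples per case.

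**Reading A: raw values are checked.** Baseline is log-normal and changes are exactly normal, with SD half the baseline SD. The entries are the share of samples in which KS with the Lilliefors correction rejects at either visit.

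| log-SD | n = 20 | n = 52 | n = 182 |
|---|---|---|---|
| 0.5 | 41% | 78% | 99.9% |
| 0.8 | 68% | 98% | 100% |
| 1.0 | 81% | 99.6% | 100% |

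A separate run over similar shapes spanned 38–84% at n = 20. The same check on the changes rejects in about 5%, and the paired t-test's error stays at 4.6–5.2%. With uncorrected critical values, the check on baseline values rejects in 1%, 9% and 19% at n = 20, but in 85–100% at n = 182. In the opposite case (near-normal raw values, changes with skewness 2), the Lilliefors check on raw values rejects in only 8–9% of samples at any n.

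**Reading B: changes are checked, n = 20.**

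| Skewness of changes | KS uncorrected | Lilliefors | Shapiro–Wilk | t-test error |
|---|---|---|---|---|
| 1.0 | 0.2% | 19% | 32% | 5.6% |
| 1.4 | 0.9% | 31% | 53% | 6.3% |
| 2.0 (exponential) | 4% | 57% | 82–83% | 8.1% |
| 6.2 (log-normal, log-SD 1) | 20% | 79% | 93% | 13.5% |

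For truly normal data the uncorrected test rejects in about 0%, against a nominal 5%.

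**Reading B at larger n.** For changes with skewness 1.0, Lilliefors rejects in 41% at n = 52 and 93% at n = 182 (uncorrected: 2% and 31%). The t-test's error is 5.4% and 4.7%, so it did not need replacing.

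**Cost of a needless switch.** With two occasions the Friedman statistic reduces to (n₊ − n₋)²/n, which is a sign test. At n = 20 it exceeds 3.84 only when at least 15 changes share a sign. Under the planning effect, P(change in the expected direction) = Φ(0.667) = 0.7475, and P(Bin(20, 0.7475) ≥ 15) = 0.61. The paired t-test has about 80% power and Wilcoxon signed-rank about 79%. At n = 182, with an effect giving the t-test 80% (0.209 SD), the same calculation gives 59% for the sign test; Wilcoxon keeps about 78%.

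**The case against.** The strongest reply is that the article condenses a fuller plan, and that 'the data' may simply mean the changes. A reader might infer that the plan tests raw values. The text does not settle this, and the two readings fail in different ways, so both failures should not be charged to one plan. What stands is that the article does fix the check, the named test and the consequence, and that each reading leaves a weakness.

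A reader might also infer that strong skew will pass unnoticed at n = 20. The documents do not support that. Q-Q plots are named alongside KS, and the simulations use the test alone. The skew that Lilliefors mostly misses (1.0 to 1.4) costs the t-test little.

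A third inference is that the KS check itself cuts power from about 80% to 60%. It does not. That loss comes mainly from Friedman being a sign test at two visits, and the words introducing Friedman leave room for Wilcoxon or a log scale.

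Finally, one might want every skewed outcome analysed as log(x + 1). The log option is already in the plan. In the setting of Reading A, a blanket log rule gave 42–77% power at n = 182 against about 80% for the t-test. That setting also yields some negative follow-up values, which minutes or cytokines cannot take, so it only illustrates the mechanism.

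**Conclusion.** The concern holds as a minor point. The rule that selects the analysis is not tied to the quantity on which the paired t-test depends, and KS is poorly suited to making the selection. Under the assumed shapes, a raw-value check with the Lilliefors correction would set aside a valid t-test in roughly 40–85% of samples at n = 20 and nearly always at n = 182. A check on changes would catch exponential skew at n = 20 in 4% or 57% of samples, depending on the KS version, against about 82% for Shapiro–Wilk. At the pooled size with Lilliefors it would reject harmless skew.

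Inflated error at n = 20 is confined to strongly skewed changes: about 8% at skewness 2, against 5.6–6.3% for moderate skew. The figures at n = 182 assume pooling, which the article does not state. The consequence is small because this is a single-arm pilot whose outcomes are called mainly descriptive, although the t-tests are still meant to evaluate the intervention's impact on health outcomes.

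**What to change.** Replace the sentence on the normality check with:

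> Distributional assumptions will be judged on the within-person changes (final minus baseline) by Q-Q plot; no Kolmogorov–Smirnov p-value will select the analysis.

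If a formal test is kept, apply Shapiro–Wilk to the changes. Use the log transformation that the section already allows only where changes are plausibly proportional, not as a general log(x + 1) rule.

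The cost is one sentence. No data, visits or sample size change. The one drawback is that the Q-Q plot calls for judgement, so the plots should be kept with the analysis record.
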